### Laboratory testing

This will include the microfilaria density, determination of plasma or serum levels or titres of *O.volvulus* specific IgG, and plasma or serum and CSF levels or titres of inflammatory markers. Markers of inflammation will be tested by ELISA or using Luminex assays. *Antibodies to HNPs such as GAD and the VGKC complex will be tested by radioimmunoassay and antibodies to* LGI-1, CASPR-2, AMPA, GABA_A_ and GABA_B_, NMDA and glycine-receptors *will be tested by cell based assays as indicated by immuno-histology on rodent brain sections* [21]*.*

### Randomisation, allocation and treatment initiation phase

Once all pre-randomisation assessments are complete, participants will be randomised to either doxycycline or placebo with a 1:1 allocation as per a computer-generated randomisation schedule stratified by skin snip test results in to four groups; A, B, C and D. The randomisation code and stratification will be prepared by an independent statistician at a data centre at Global Health Uganda. The study pharmacy assistant will email the independent data centre with the study ID and the microscopy results of the skin snip for *O.volvulus* and the data centre statistician will allocate the participant to the study arms*.*

Eligibility criteria for randomisation are fulfilment of the enrolment criteria and the dose of sodium valproate rationalised to at least 20 mg/kg/day (maximum 35 mg/kg/day) if the patient still experiences one or more tonic clonic seizures a month. Participants reported to be unable to swallow capsules, those already enrolled (or who will enrol) into another trial, and those who withdrew consent since enrolment, will be excluded from randomisation.

The intervention drugs (doxycycline capsules [Azudox®] and placebo) will be obtained from Kampala Pharmaceutical Industries, Uganda. The active drug and the placebo will be labelled with the study code by Kampala Pharmaceutical Industries in collaboration with the independent statistician. Each Azudox capsule contains doxycycline hyclate equivalent to 100 mg of doxycycline base. In the treatment of *Onchocerca volvulus,* doxycycline is given in doses of 100-200 mg/day for 4–6 weeks [31]. We chose the lower dose of 100 mg/day since most participants will be adolescents many of who will also have wasting. With an average weight of 33 kg, we anticipate this dose will translate to ~ 3 mg/kg/day. The two interventions will be identical in the number of capsules (one) per day and timing. The drug administration procedures will also be identical. Both the caretakers and investigators will be blinded. However, in the event of medical emergency un-blinding of an individual participant to the PI or safety monitoring teams may be conducted. Otherwise, all treatment allocations will only be disclosed after the data is locked and a statistical analysis plan is in place.

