### Sample size

From our pilot studies, ~ 50% of patients with prevalent nodding syndrome had antibodies to a HNPs and ~ 60% to leiomodin [2, 22]. We hypothesise that among patients with new onset nodding syndrome (symptoms < 12 months), six weeks’ therapy with doxycycline will cause a 50% reduction in the proportion of patients with and the levels or titres of antibodies to HNPs (a reduction from 50 to 25% compared to placebo) at 24 months. In Uganda, however, there has been no incident cases of nodding syndrome since 2014. It is anticipated that the intervention may not be as efficacious in patients with established symptoms (i.e. patients with symptoms ≥12 months) and the effect on antibodies would be smaller (an anticipated 40% reduction from 50 to 30%). To demonstrate this effect at 80% power and 5% level of significance and allowing for 10% losses to follow up, we will need to recruit a total of 230 patients with established symptoms (115 in either arm).

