### Statistical analysis

Analysis will be by intention to treat. The analysis will compare the proportions of patients testing positive for and the levels or titres of antibodies to HNPs or leiomodin at baseline and at 24 months in both arms. Both crude (unadjusted) and adjusted effect estimates will be computed. The chi square test will be used to compare proportions of children with the different antibodies in the two arms; the Students t-test will be used for means of normally distributed data and the Mann-Whitney U test for skewed data. We will also determine the mean change or reduction in the levels or titres of the antibodies and inflammatory markers with the intervention. Time to event (e.g. to seizure resolution) will be measured from the date of randomisation using Kaplan Meyer Survival analysis and by Cox regression analysis. For the cognitive tests, in addition to classification as impaired or not (in comparison to norms determined from unaffected sibling controls in the concurrent case control study), we will also measure mean improvements in scores. The rates determined will be adjusted for age, HIV infection, weight for height z scores and corrected for multiple testing. We will examine safety (serious adverse events and adverse events) and assess compliance and the factors for poor compliance.

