## Discussion

The goal of this study is to understand the pathogenesis of, and to develop specific interventions for, nodding syndrome. Currently, there is no specific treatment for nodding syndrome. The only available treatment is a package of therapies aimed at symptomatic relief [32]. This project has the potential to advance the understanding of nodding syndrome, allow definitive diagnosis and gain insight into potential new approaches for treatment and prevention. If evidence of neuro-inflammation is found and/or specific autoantibodies, immune-modulatory therapies, for example with high dose steroids, may be considered at symptom-onset [2]. In addition, a biologic association between nodding syndrome and *O.volvulus* would allow escalation of treatments and prevention. If a potential use for doxycycline, as treatment for nodding syndrome is observed, it would also be a proof of principle that treatment is possible in older children. Such a strategy could also be explored for younger newly affected children. It is important to point out that the proposed use of doxycycline is based on its effectiveness as treatment for adult *O. volvulus.* Its success will not depend on *Wolbachia* playing a direct role in the pathogenesis of NS (although it may), rather, it is a test of the broader hypothesis that *O.volvulus* plays a role in the pathogenesis of NS.

The approach of using doxycycline is supported by the facts that (1) *O.volvulus* infection has had the most consistent association with nodding syndrome out of many potential risk factors examined to date [33]; (2) doxycycline is a cheap and safe drug and the only curative treatment for adult *O.volvulus* currently available [23]; (3) a direct intervention has considerable advantages over epidemiological association studies in elucidating causality. This is thus a low risk but potentially high gain approach: a positive result would have great significance in understanding both pathogenesis and offering a hope of treatment, whilst a negative result would still be helpful in indicating that whatever the pathogenesis, a simple approach to reducing *O.volvulus* load may not necessarily offer an advantage.

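### Randomisation is stratified by skin-snip result, but the stated tests and covariate list leave that factor out, which can make the efficacy comparison mildly conservative

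*Protocol article*

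**What the plan says.** The section on randomisation, allocation and treatment initiation states that "participants will be randomised to either doxycycline or placebo with a 1:1 allocation", using a "computer-generated randomisation schedule stratified by skin snip test results in to four groups; A, B, C and D". No other stratification factor is named. The data centre receives the skin-snip microscopy result before it allocates each participant.

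The Statistical analysis section states that "The chi square test will be used to compare proportions of children with the different antibodies in the two arms". Means are to be compared by t-test, and skewed data by Mann-Whitney test. Both crude and adjusted estimates are planned, and the rates are to be "adjusted for age, HIV infection, weight for height z scores". The skin-snip stratum is in neither the tests nor that list.

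The Sample size section assumes "an anticipated 40% reduction from 50 to 30" per cent in antibody positivity, and continues: "To demonstrate this effect at 80% power and 5% level of significance and allowing for 10% losses to follow up". This leads to 230 participants, 115 per arm.

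**The concern.** Stratified allocation makes the arms more alike on the stratification factor than simple randomisation would. If that factor predicts the outcome, the true variability of the difference between arms is smaller than an unstratified test assumes. The crude standard error is then too large, the confidence interval too wide and the test conservative. The usual remedy is to analyse by the factors used in the randomisation.

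This does not rest on the article's silence. The article names its tests and covariates. It lists three variables that were not used in allocation and omits the one that was.

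The trial's hypothesis gives a reason to expect the factor to matter: antibodies raised against *O. volvulus* or *Wolbachia* are thought to cross-react with neuron proteins. Parasite status could therefore be related to antibody positivity. At stake is some precision that the design has already provided for and the stated analysis would not use.

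**Working it through.** **1. The plan's own sample size.** Inputs from the Sample size section: 50% v 30%, power 80%, alpha 5% (taken as two-sided), 10% loss.

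- Uncorrected n per arm = [1.96·√(2·0.4·0.6) + 0.8416·√(0.5·0.5 + 0.3·0.7)]² / 0.2² = 93.
- With continuity correction: (93/4)·[1 + √(1 + 4/(93·0.2))]² = 102.8, so 103.
- After 10% loss: 103/0.9 = 114.4, so 115 per arm and 230 in total.

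The stated 230 is reproduced. About 115 × 0.9 = 103.5 per arm are evaluable; 104 is used below so that the strata divide evenly.

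**2. Assumptions that the document does not supply.** The article gives neither stratum sizes nor the link between skin-snip result and antibody status. I assume two equal strata, balanced by arm, with placebo positivity averaging 50%, and vary the gap between them.

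**3. Standard error with no treatment effect.** The crude variance per person is 0.5 × 0.5 = 0.25. The correct value is the average of p(1−p) within strata. The standard error (SE) of the difference is √(2·variance/104).

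- 50%/50%: variance 0.25, SE 0.0693, no excess.
- 65%/35%: variance 0.65 × 0.35 = 0.2275, SE 0.0661. The crude SE is too large by √(0.25/0.2275) = 1.048, about 5%.
- 75%/25%: variance 0.75 × 0.25 = 0.1875, SE 0.0600. The excess is √(0.25/0.1875) = 1.155, about 15%.

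The crude test therefore behaves as if its critical value were 1.96 × 1.048 = 2.05 or 1.96 × 1.155 = 2.26. In large samples these give type I errors of about 4.0% and 2.4%.

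**4. Simulation.** 40,000 trials, 104 per arm, a 40% relative reduction in each stratum, crude chi-square against Cochran-Mantel-Haenszel (CMH):

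| Placebo positivity | Crude type I error | Crude power | CMH power |
|---|---|---|---|
| 50%/50% | 4.5% | 84.9% | 84.7% |
| 65%/35% | 3.7% | 85.5% | 86.4% |
| 75%/25% | 2.0% | 87.5% | 90.6% |

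Repeat runs moved the crude type I error at 65%/35% between 3.5% and 3.7%. Where the strata are prognostic, CMH stays at about 5%. The simulated crude values lie slightly below those in step 3 because the counts are discrete.

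**5. Four strata, as in the plan.** Four equal strata with placebo positivity spread evenly over the range shown:

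| Range | Crude type I error | Crude power | CMH power | Crude SE ÷ stratified SE (with effect) |
|---|---|---|---|---|
| all 50% | 4.6% | 85.0% | 84.8% | 0.0662/0.0652 = 1.02 |
| 40–60% | 4.1% | 85.1% | 85.3% | 0.0662/0.0647 = 1.02 |
| 30–70% | 3.5% | 85.5% | 86.4% | 0.0662/0.0630 = 1.05 |
| 15–85% | 1.8% | 87.7% | 91.2% | 0.0662/0.0582 = 1.14 |

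The 2% in the first row reflects only small-sample estimation of the stratified SE. The pattern matches two strata.

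**The case against.** The strongest reply is that the loss is conditional and small. No passage shows that skin-snip result predicts antibody status. If it does not, stratifying gains nothing, and even a 65%/35% split costs only about 1 power point. The error runs in the safe direction. All of this stands, and it limits the point to efficiency and good practice.

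A reader might go further and infer that the plan hides the infected participants in whom the drug could work. Infection is not an entry criterion, while the Discussion says that "the proposed use of doxycycline is based on its effectiveness as treatment for adult" *O. volvulus*. The documents do not support that reading, for four reasons.

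- The article does not rule out a subgroup or interaction analysis. That is ordinary content for a statistical analysis plan, which is not shown.
- Skin-snip microscopy detects microfilariae. The Background says that ivermectin kills these but that the adult worm has no specific drug treatment, so a negative snip does not show that adult worms are absent.
- Sizing on an average effect is not an error. The Sample size section starts from rates in prevalent patients not selected for infection, and lowers the expected reduction from 50% to 40% for established disease.
- Any dilution figure depends on unknowns. Suppose half the participants are infected and only they respond. If baseline positivity is 50% in everyone, the pooled comparison is 50% v 40%, with 30% power at 103 per arm. If the infected have 65% and the others 35%, the treated rate is (0.39 + 0.35)/2 = 37% and power is about 48%. At 75%/25% it is (0.45 + 0.25)/2 = 35% and about 60%. The document does not say which applies, or what share is infected.

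**Conclusion.** The mismatch between design and analysis is real: allocation is stratified by skin-snip result, and the named tests and covariates omit it. The consequence is conditional. In the two-strata scenarios the cost runs from nothing (strata not prognostic), through about 1 power point with type I error about 3.5% (65%/35%), to about 3 points with type I error about 2% (75%/25%). The most extreme four-strata case, 15–85%, costs 3.5 points (91.2 − 87.7).

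These figures assume equal strata, balance by arm, 104 evaluable per arm and the planned 40% relative reduction in every stratum. The planned test remains valid. Type I error is not inflated and the sample size of 230 does not change.

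**What to change.** In the Statistical analysis section, use the skin-snip randomisation stratum in the efficacy comparisons: CMH for proportions, and a stratum term in the models for antibody levels and other outcomes. Add the stratum to the listed covariates and state in advance how sparse strata will be collapsed. Keep all randomised participants as the primary population.

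As a supportive step only, report the treatment effect by baseline skin-snip status. A stratum covariate alone would not show a differential effect; that needs stratum-specific estimates or a treatment-by-stratum interaction. State alongside them that power is limited and that a negative snip does not exclude adult worms.

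The cost is a change of wording plus one supportive analysis. The stratum is already recorded at randomisation, and nothing changes in recruitment, treatment or follow-up. The article keeps allocations undisclosed until the data are locked and an analysis plan is in place, so the change can be made blind.

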### Administration of the trial medication

The intervention drugs will be packaged in capped plastic containers each containing 50 capsules (42 + 8 extra capsules). Treatment will be initiated in hospital and continued at home. The first dose will be administered under direct observation at the clinic. Participants and their caretakers will then be carefully instructed about taking subsequent doses before they return home. Each participant will be visited at home at 2, 4 and 6 weeks for adherence and safety monitoring (detailed below). Parents/carers will be reminded weekly through mobile phone contact to ensure the participants take the assigned interventions.

The product will be taken with water between 6.00–9.00 am and at about the same time each day. Should a carer forget to give the dose at the set time, they will be advised to give it as soon as this is realised and to continue the recommended regimen until the dose is completed. Participants will be observed for at least 30 min after taking the medication. Should they vomit within 30 min of receiving the intervention drug, the full dose will be re-administered. Such vomiting will be documented. On a single day, repeat dosing will be attempted once. The eight additional capsules in each pack are to cater for such eventualities.

### Intervention phase, adherence and safety monitoring

To minimise losses to follow up and aid follow up visits in the home, a contact cell phone number will be recorded prior to discharge and the participants be accompanied home by a home visitor who will also draw a sketch map to document the route home and obtain the Global Positioning Satellite (GPS) data of the home.

During each visit, the home visitor will document adverse events, ensure seizures are documented in a seizure diary, conduct pill counts and counsel on adherence. Participants with < 80% adherence at weeks 2 and 4 will be visited again the following week and have additional counselling. Intake of the study drug on the day of the home visit will be directly observed. Participants will continue to attend the 1–2 monthly non-study clinical visits.

Adverse events (AEs) and serious adverse events (SAEs) will be documented following ICH GCP principles and all SAEs reported to the DSMB and ethics committees. If children are found to be ill during these home-visits they will be referred to the study clinic for further evaluation as part of the unscheduled visits.

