### Unscheduled visit (passive follow-up)

Parents will be instructed to bring the participants to the study clinic for any suspected illness. The ‘chief complaint’ and ‘diagnoses’ will be recorded using a standard list based on the International Classification of Disease (ICD-10) for children. Consent will be sought from parents or guardians of participants who die for a formal post mortem or verbal autopsy if the post-mortem is not possible.

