### Secondary safety outcomes

Secondary safety outcome measures will be the incidence rate of serious adverse events and adverse events up to 24 months after enrolment.

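### Extra home visits for poor adherers make adverse-event enquiry during dosing depend on adherence: a minor risk of unequal ascertainment between arms

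*Protocol article*

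**What the plan says.** All participants have the same scheduled contacts during dosing (Protocol article, Administration of the trial medication): "Each participant will be visited at home at 2, 4 and 6 weeks for adherence and safety monitoring". Everyone also receives phone calls, whose stated purpose is dosing: "Parents/carers will be reminded weekly through mobile phone contact to ensure the participants take the assigned interventions".

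The section on the intervention phase, adherence and safety monitoring covers what happens at a home visit: "During each visit, the home visitor will document adverse events". It then adds the adherence rule: "Participants with < 80% adherence at weeks 2 and 4 will be visited again the following week and have additional counselling". Nothing exempts these additional visits from AE recording.

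Outside the home visits there is open access to the clinic (Unscheduled visit): "Parents will be instructed to bring the participants to the study clinic for any suspected illness". The safety outcome is the "incidence rate of serious adverse events and adverse events up to 24 months after enrolment" (Secondary safety outcomes). It is not restricted to events found at scheduled contacts.

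**The concern.** A between-arm AE comparison is fair when both arms are asked equally often and in the same way. Here the number of home enquiries in the dosing weeks is three for a good adherer and four or five for a poor one. Adherence is measured after randomisation and can be affected by treatment, so randomisation does not balance it. Blinding stops staff from favouring an arm, but it does not stop a difference in tolerability from becoming a difference in adherence and hence in visits.

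The dosing weeks are the only period in which study drug is given, so this is where a comparison of mild side effects tells the reader most. An imbalance in enquiry would tilt that comparison against the arm with worse adherence, whichever arm that is. The events found at extra visits are real. The distortion would come from similar events going unrecorded among participants who were asked less often.

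**Working it through.** The article states no figure for AE ascertainment, so there is none to reproduce.

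**Inputs from the article.** Scheduled home visits at weeks 2, 4 and 6; extra visits the week after a failed adherence check, that is, weeks 3 and 5; 1:1 allocation.

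**Assumed inputs (not in the article).** The share *q* of poor adherers in each arm, and the probability *r* that a carer still reports an event 14 days after it occurred.

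**Step 1: contacts.** If each failed check triggers a visit and poor adherers fail both, mean home enquiries are 3 + 2*q*. One poor adherer has 5 instead of 3 (5/3 = 1.67). For 30% versus 10%: 3.6/3.2 = 1.125. This would be the AE rate ratio only if recorded events rose in proportion to visits.

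**Step 2: what the extra visits add.** The week 3 and week 5 visits lie inside intervals that the week 4 and week 6 visits already cover, so they add only events that would have been forgotten by then. Let reporting at the next visit decline exponentially with the gap, with events spread evenly over six weeks.

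- Fraction reported from a two-week interval: A = (1 − r)/(−ln r). On the scheduled visits alone, f0 = A.
- Fraction reported from a one-week interval: B = 2(1 − √r)/(−ln r). With both extra visits, f1 = (A + 2B)/3.
- Rate ratio: [(1 − q1)f0 + q1·f1] / [(1 − q2)f0 + q2·f1], where q1 is the arm with worse adherence.

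| Recall at 14 days | f0 | f1 | 10% v 5% | 20% v 10% | 30% v 10% | 40% v 20% |
|---|---|---|---|---|---|---|
| 100% | 1.000 | 1.000 | 1.000 | 1.000 | 1.000 | 1.000 |
| 80% | 0.896 | 0.930 | 1.002 | 1.004 | 1.007 | 1.007 |
| 60% | 0.783 | 0.849 | 1.004 | 1.008 | 1.017 | 1.017 |
| 40% | 0.655 | 0.753 | 1.007 | 1.015 | 1.030 | 1.029 |

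With equal shares (10% v 10%) the ratio is 1.000 in every row. Worked case, 40% recall, 30% v 10%: (0.7 × 0.655 + 0.3 × 0.753)/(0.9 × 0.655 + 0.1 × 0.753) = 1.03.

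**Step 3: two variations.**

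- *Poor adherers have more events.* Step 2 gives everyone the same AE rate. If poor adherers have three times the rate, the fraction of events recorded at 40% recall is (0.7 × 0.655 + 0.9 × 0.753)/1.6 = 0.710 in the 30% arm and (0.9 × 0.655 + 0.3 × 0.753)/1.2 = 0.679 in the 10% arm. The true rate ratio is then multiplied by about 1.045.
- *The trigger means failing both checks.* The wording allows this reading, which gives one extra visit, at week 5. The fraction for a poor adherer becomes (2A + B)/3. At 40% recall, A = 0.655 and B = 0.802, so the fraction is 0.704, and 30% v 10% gives (0.7 × 0.655 + 0.3 × 0.704)/(0.9 × 0.655 + 0.1 × 0.704) = 1.015.

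**Step 4: 24-month window.** Adding the four follow-up assessments at 6, 12, 18 and 24 months, and supposing AEs are asked about at each, mean contacts are 7 + 2*q*. Even under proportionality, 30% v 10% gives 7.6/7.2 = 1.06 instead of 1.125. Passive clinic reporting would dilute the effect further.

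**The case against.** The visit rule is the same in both arms and is applied blind. The article gives no adherence rate by arm and nowhere says that doxycycline lowers adherence. Its provision for vomiting does not fill that gap: a vomited dose is repeated from the spare capsules, and adherence is checked by pill count, so vomiting tends to raise counted adherence. Poor adherers also take less drug, which may work the other way. This stands: neither the existence nor the direction of an imbalance can be derived from the text.

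A reader might infer that the doxycycline AE rate will be inflated by 6% to 19%, from contact ratios of 3.4/3.2, 3.6/3.2 and 3.8/3.2 (1.06, 1.13 and 1.19). The article does not support that. Those are ratios of visits, not of events, and they presuppose both worse adherence on doxycycline and recording in proportion to visits.

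It can also be said that describing the calls as reminders does not prove that AEs go unnoted in them, and that the full protocol or analysis plan may deal with the source of reports. That is fair, and it is one reason to rate the point as minor. But the visit schedule and the purpose of the calls are fixed in the article as written, and no later analysis can recover enquiries that were never made.

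**Conclusion.** The point holds as a minor one. AE enquiry during dosing depends on adherence after randomisation, and the contacts that everyone has are not described as evening this out. If adherence is equal between arms, or recall over two weeks is complete, there is no distortion. Otherwise it is probably a few per cent at most on the six-week rate ratio: about 1.007 to 1.03 for an assumed 30% v 10% poor adherers with 80% to 40% recall, and up to about 1.045 if poor adherers also have three times the events. The arm affected is unknown. These figures rest on assumed adherence shares and an assumed exponential recall curve, since the article supplies neither.

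The effect on the 24-month safety outcome is smaller. Mild events are the ones mainly concerned, and serious events are unlikely to depend on one more home enquiry. The primary antibody outcome is unaffected.

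**What to change.** 1. In the weekly phone call already made to all participants during dosing, ask the same short AE question of everyone. This largely evens out enquiry between good and poor adherers and leaves the counselling visits as they are.
2. Add a field to the AE form for the source of each report: scheduled visit, adherence-triggered visit, phone call, or clinic attendance.
3. Keep all AEs in the main between-arm safety rate. Add a sensitivity analysis that omits non-serious events first reported at adherence-triggered visits. Dropping these events from the main rate would discard real events, possibly in the participants who tolerate treatment least, so the omission belongs only in the sensitivity analysis.

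The cost is a few minutes per call, one form field and one extra analysis. The downside is somewhat more minor AEs to record in both arms.
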